#### Exclusion criteria

Participants will be excluded if they meet any of the following criteria:Participation in another randomised controlled trial that could conflict with this study.End-stage disease with an estimated life expectancy of < 6 months.Inability to understand or adhere to the intervention due to altered mental status, severe cognitive impairment, or severe visual, hearing, or language impairment.Unable to complete follow-up procedures (e.g., no reliable contact information for the participant/caregiver).Medical or clinical conditions that would preclude adherence to the dietary intervention or safe participation (e.g., pathological eating disorder, severe malnutrition, morbid obesity, or other conditions judged by the investigator).Food allergies or intolerances to key components of the study diet, or other conditions that prevent consumption of the assigned diet.Use within the past 4 weeks of antibiotics, probiotics, multivitamins, or dietary supplements (including fish oil, omega-3 fatty acids, herbal supplements, calcium, or vitamin D).Use of nonsteroidal anti-inflammatory drugs (NSAIDs), antihistamines, or immunosuppressive medications, or inability to refrain from these substances during protocol-specified peri-sampling windows (as defined in the protocol).Heavy smoking (> 20 cigarettes/day) or excessive alcohol consumption (> 2 standard drinks/day), or unwillingness to abstain from smoking and alcohol for the duration of the study.Significant comorbidities such as autoimmune disease, haematological disease, cardiovascular disease, or active infection, which in the investigator’s judgement would compromise safety or study integrity.

#### Criteria for withdrawal/discontinuation

Participants may be withdrawn or discontinue the intervention if:The participant withdraws consent.The participant’s clinical condition deteriorates and continued participation is no longer appropriate.A serious adverse event occurs (e.g., hypoglycaemia, weight loss > 2 kg/week, food allergy).Adherence remains consistently poor.Scheduled visits are missed for unforeseen reasons.

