### Sample size {19}

Sample size was estimated using the Tests for Two Proportions module in PASS 2025 for the primary endpoint, defined as experiencing any prespecified CTCAE gastrointestinal toxicity of grade ≥ 2. Given two prespecified primary comparisons, a Bonferroni-adjusted two-sided α of 0.025 and 80% power were applied. Based on Souza et al. [24], the assumed proportions were 0.176 in the intervention group and 0.533 in the control group. Under these assumptions, 30 evaluable participants per group are required for each primary comparison. To account for an anticipated 20% loss to follow-up, this was rounded up to 38 participants per arm (total N = 114; 1:1:1).

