### Plans to promote participant retention and complete follow-up {25b}

To promote retention and complete follow-up, participants will receive enrollment education and written materials (brochures) and will be reminded of scheduled assessments via WeChat messages, reminder cards, and telephone calls. Whenever possible, follow-up will be aligned with routine chemotherapy-related contacts, with flexible scheduling within predefined visit windows. Missed visits will trigger repeated contact attempts, and reasons for missed visits, discontinuation, or protocol deviations will be documented. Participants who discontinue or deviate from the allocated dietary intervention will be encouraged to remain in follow-up; every reasonable effort will be made to collect key outcome and safety data at the scheduled time points to support intention-to-treat analyses. If a participant withdraws consent for further data collection, no additional data will be collected, and the withdrawal reason will be recorded if the participant agrees.

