### Who will be included in each analysis {27b}

The primary analysis will follow the intention-to-treat (ITT) principle, including all randomised participants and analysing them in the groups to which they were allocated, regardless of adherence or protocol deviations. A per-protocol sensitivity analysis will be conducted excluding participants with major protocol violations and/or not meeting prespecified adherence criteria. Safety analyses will include all participants who received any component of the assigned intervention/comparator.

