### How missing data will be handled in the analysis {27c}

Every effort will be made to minimise missing data through the retention procedures described above. For longitudinal outcomes, mixed-effects models using maximum likelihood estimation will be the primary approach and can accommodate missing outcome data under a missing-at-random assumption. If additional handling is required (e.g., substantial missingness in key secondary outcomes), multiple imputation will be applied using prespecified models incorporating baseline variables, stratification factors, and available outcome history; results will be compared with complete-case analyses as sensitivity checks. For microbiome/metabolomics features, no imputation will be performed for unavailable samples; analyses will be based on available specimens, with missingness patterns summarized and sensitivity analyses performed where appropriate.

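### The withdrawal list does not separate stopping the diet from leaving follow-up, so poor adherence or missed visits could end outcome collection, against the retention and intention-to-treat text

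*Protocol article*

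**What the plan says.** Criteria for withdrawal/discontinuation gives one list for two different things, being withdrawn and stopping the intervention. Two of its five entries are "Adherence remains consistently poor" and "Scheduled visits are missed for unforeseen reasons".

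Other sections point towards retention:

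- Section {15b} says that stopping or changing the diet does not by itself take a participant out of follow-up, and that outcomes are still assessed where possible. It has its own reasons for stopping or modifying the diet, and names neither poor adherence nor missed visits.
- Section {25b} says: "Participants who discontinue or deviate from the allocated dietary intervention will be encouraged to remain in follow-up". Missed visits lead to renewed attempts at contact. Collection ends when the participant withdraws consent to further data collection.
- Section {27b} defines the primary analysis as "including all randomised participants and analysing them in the groups to which they were allocated, regardless of adherence or protocol deviations".

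The confirmatory endpoint (Outcomes {16}) is one yes/no value per participant: any listed gastrointestinal toxicity of grade 2 or worse during follow-up, assessed after baseline at T1, T2, T4 and T6. Section {27a} tests it by logistic regression. Section {27c} makes mixed models the main approach to missing data for longitudinal outcomes, and adds: "If additional handling is required (e.g., substantial missingness in key secondary outcomes), multiple imputation will be applied using prespecified models".

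**The concern.** A site that follows the withdrawal list could take a non-adherent participant, or one who missed a visit, out of the study. A site that follows section {25b} would keep the same person and go on collecting data. Only the second course serves the analysis in section {27b}.

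The adherence entry matters most. The Discussion says that nausea, anorexia, mucositis, taste changes and diarrhoea may lead participants away from the assigned diet. All of these except taste changes are components of the primary endpoint. Withdrawal for poor adherence could therefore remove people because of the toxicity being counted. It could also act unequally: the article describes dietary targets for the plant-based arm and sachet counts for the formula arm, but no comparable adherence measure for the conventional arm. That last step is an inference, and the documents do not predict which arm would lose more.

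The secondary issue is how missing values of the confirmatory endpoint are handled. A logistic regression with one record per participant drops anyone without a value, and the mixed-model sentence does not apply to it. Multiple imputation could apply, but it is conditional and its only example is a secondary outcome.

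**Working it through.** **1. The plan's own figures.** Sample size {19} states that "a Bonferroni-adjusted two-sided α of 0.025 and 80% power were applied", that "the assumed proportions were 0.176 in the intervention group and 0.533 in the control group", and that "30 evaluable participants per group are required for each primary comparison". With the unpooled two-proportion formula:

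n = (z₀.₉₈₇₅ + z₀.₈₀)² × [p₁(1−p₁) + p₂(1−p₂)] / (p₁−p₂)²

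= (2.241 + 0.842)² × (0.176×0.824 + 0.533×0.467) / 0.357² = 29.38, rounded up to 30.

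Allowing for 20% loss, 30/0.80 = 37.5, rounded up to 38 per arm and 114 in all. The stated figures reproduce. They mean that the plan expects about 8 of 38 per arm, or 0.20 × 114 ≈ 23 in total, to lack an evaluable primary outcome.

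**2. The passages side by side.**

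| Situation | Withdrawal list | Other sections |
|---|---|---|
| Persistently poor adherence | May be withdrawn or stop the intervention | {25b}: encouraged to stay in follow-up; {27b}: analysed regardless |
| Missed visit | May be withdrawn or stop the intervention | {25b}: repeated contact attempts |
| End of data collection | Not separated from stopping the diet | {25b}: when consent for further collection is withdrawn |

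Reading the list as covering only the diet would remove the conflict, but it fits poorly. The lead-in names withdrawal and stopping the intervention as alternatives, section {15b} already covers the diet, and a missed visit is a more natural reason to leave a study than to stop a diet.

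**3. Possible bias (assumed inputs, not from the documents).** Suppose there is no true effect, with risk 0.40 in both arms. Let 30% of the plant-based arm and 10% of a comparator be lost (average 20%, as planned), with risk 0.70 among those lost and none of their events recorded.

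- Complete case: (0.40 − 0.30×0.70)/0.70 = 0.271, against (0.40 − 0.10×0.70)/0.90 = 0.367. This is a spurious benefit of 9.5 points.
- Lost participants scored as non-events: 0.40 − 0.21 = 0.19, against 0.40 − 0.07 = 0.33. This is 14 points.
- With the two loss rates exchanged, both become spurious harms of the same size.
- If half of the lost participants' events had been recorded before loss, the second gap becomes (0.40 − 0.105) against (0.40 − 0.035), or 0.295 against 0.365. This is 7 points.

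The planned effect is 0.533 − 0.176 = 0.357, about 36 points.

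**4. How much the handling rule matters (assumed counts).** Take 5/30 against 16/30 events observed, close to the planned rates, with 8 missing per arm. Chi-square p-values, against the 0.025 threshold, are:

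| Handling of missing outcomes | Events | p |
|---|---|---|
| Complete case | 5/30 v 16/30 | 0.003 |
| All non-events | 5/38 v 16/38 | 0.005 |
| All events | 13/38 v 24/38 | 0.012 |
| Events in the plant-based arm only | 13/38 v 16/38 | 0.48 |
| Events in the comparator only | 5/38 v 24/38 | <0.001 |

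Equal treatment of both arms leaves the conclusion unchanged here. Only the extreme assumption against the plant-based arm overturns it.

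**The case against.** The strongest reply is that the plan already favours retention. The withdrawal list is permissive and does not say that data collection stops, while sections {15b} and {25b} keep people in follow-up, the latter expressly to support the intention-to-treat analysis. Daily remote contact in all arms, adverse events graded at scheduled contacts from T0 to T7, and assessment by telephone or WeChat mean that a missed visit need not mean missing toxicity data. The multiple imputation sentence gives an example, not a limit, and its model already uses outcome history. The level of imputation, the scoring of partly observed participants and any tipping-point analysis may properly sit in a SAP that is not shown.

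Most of this stands, and it rules out stronger readings. A reader might infer that the intention-to-treat analysis cannot be delivered, or that the primary result will be a complete-case analysis under another name. The documents do not support either. Nor do they anywhere score missing participants as non-events. A reader might also take the Discussion to say that toxicity causes missed visits, but it speaks only of departures from the diet.

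The reply does not remove the conflict. A permissive rule can still be used, and a later SAP cannot recover outcomes that were never collected.

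**Conclusion.** The point holds as a conflict to be reconciled. The withdrawal list allows participants to be withdrawn for poor adherence or missed visits without separating the diet from follow-up, contrary to sections {15b}, {25b} and {27b}. For the adherence entry, the Discussion supports a link to the outcome; for missed visits, such a link would be inference.

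The secondary point is smaller: the missing-data section does not name the one confirmatory binary endpoint, although about 8 of 38 per arm are expected to be lost.

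The documents do not determine the size of any bias. The 9.5 and 14 points rest on an assumed base risk, assumed loss rates, an assumed risk among those lost and no event recorded before loss. The 14 points also need a scoring rule that the plan does not state. Because T1 and T2 fall in the first week, early events would often be recorded before loss, which would reduce these figures. Their direction depends on which arm loses more. The sample size is unaffected.

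**What to change.** 1. Reword Criteria for withdrawal/discontinuation so that stopping the dietary programme and leaving follow-up are separate. State that poor adherence and missed visits do not end outcome data collection, which under section {25b} stops only when consent for further collection is withdrawn. This takes no position on when the diet itself should be stopped.
2. In section {27c} or the SAP, name the confirmatory endpoint and extend to it the multiple imputation already described, using arm, baseline variables, site, sex and the observed visit grades. Count any observed follow-up grade 2 or worse as an event, whatever is missing later. Report complete case as a sensitivity analysis. Multiple imputation is one sound choice among several, and the remaining detail belongs in the SAP.

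The cost is an amendment to one list, a sentence or two on missing data, a note to the two sites and modest programming. No extra patients or visits are needed. The first item is best done now: Trial status reports 7 enrolled as of 23 January 2026, so few participants have been exposed to the ambiguous rule.

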### Eligibility criteria for sites and those delivering interventions {14b}

The trial will be conducted at two hospital sites: West China Fourth Hospital, Sichuan University and The Seventh People’s Hospital of Chengdu, both of which are tertiary hospitals with established oncology departments. These sites must have the necessary infrastructure to administer FOLFOX chemotherapy as part of routine care for CRC patients and be equipped to deliver dietary interventions according to the trial protocol. Sites must also obtain local ethical approval and adhere to the study’s protocol, ensuring compliance with ethical standards and local regulations.

Individuals delivering the dietary interventions must have relevant qualifications and experience in oncology nutrition. They should be trained in providing plant-based dietary interventions and be capable of delivering the intervention as outlined in the protocol. All intervention providers will undergo study-specific training to ensure consistency in their approach, which includes dietary guidelines, participant engagement, and monitoring adherence. These individuals must be able to effectively communicate with participants, support adherence, and manage any questions or concerns related to the dietary intervention.

### Additional consent provisions for collection and use of participant data and biological specimens {32b}

In addition to the primary consent for participation in the study, participants will be asked for additional consent to collect and use their biological specimens (e.g., blood, stool samples) and data (e.g., inflammatory biomarkers, metabolic indicators) for ancillary studies. These specimens and data will be used solely for the purposes of this study and related research approved by the institutional ethics committee.

Participants will be informed about the storage, handling, and future use of their samples. Biological specimens will be stored at designated facilities under appropriate conditions (e.g., −80 °C storage for biological samples). Biological specimens and datasets will be labelled with unique study Identifiers (IDs) only. The linkage file between personal identifiers and study IDs will be stored separately with restricted access. Samples will be processed and analysed in a de-identified manner, and only aggregated results will be reported. Participants may withdraw consent for future use of stored specimens at any time, without affecting their participation in the main trial.

## Intervention and comparator

### Intervention and comparator description {15a}

This is a multicentre, stratified, randomised controlled trial comparing three different dietary interventions for CRC patients undergoing FOLFOX chemotherapy: plant-based dietary intervention, conventional diet, and oncology nutritional formula. Each group will receive a 6-week dietary intervention during their chemotherapy cycle.

To minimise non-specific (attention/support) effects across groups, the frequency and mode of participant contacts will be standardised across all three arms. All participants will receive: (i) a structured face-to-face education session at baseline during chemotherapy admission (T0), and (ii) daily remote follow-up throughout the 6-week intervention period (telephone/WeChat) delivered according to a prespecified checklist, primarily to record daily dietary intake and monitor symptoms/adverse events. Brief reinforcement will also be provided during inpatient chemotherapy visits when applicable. Unscheduled contacts for symptom management are permitted in all groups and will be documented. Daily contacts are primarily for data capture and safety monitoring; no additional individualized dietary counselling beyond the allocated programme will be provided unless clinically indicated.

The plant-based diet will be based on the latest evidence for nutritional and dietary interventions in managing CIGT. The diet will include fruits, vegetables, whole grains, nuts, and anti-inflammatory beverages such as green tea, soya milk, and peanut-legume juice. It will emphasize reducing red and processed meat intake and limit fish consumption. Participants will also be encouraged to follow the Dietary Guidelines for Chinese Residents [17], which include recommendations on fluid intake (1,500–1,700 ml/d), limited salt (< 5 g/d), and oil (25–30 g/d). Weekly food supplies, printed materials, and cooking videos focused on plant-based nutrition will be provided to support adherence. Quantitative targets (intervention “dose”) were prespecified to operationalize the plant-based dietary strategy: (i) vegetables and fruits ≥ 500 g/d; (ii) whole grains 70–90 g/d and legumes ≥ 1 serving/day on most days; and (iii) red and processed meat ≤ 500 g/week (fish, if consumed, limited to ≤ 300–450 g/week). These targets will be reinforced during follow-up and assessed using diet records and Food Frequency Questionnaire (FFQ)-based scoring.

The conventional diet group will receive standard dietary education and care based on the Dietary Guidelines for Chinese Residents [17]. This includes education materials and guidance according to commonly accepted oncology dietary practices. Participants will not receive individualized dietary counseling unless they seek advice regarding chemotherapy-related symptoms.

The oncology nutritional formula group will receive a commercially available oncology complete nutritional formula. The formula contains protein (including essential amino acids), fat (including essential fatty acids), vitamins (A, C, and E), and minerals. Participants will dissolve one pouch (20 g) in 100 mL of warm water and consume it twice daily for 6 weeks (target dose: 2 pouches/day). Adherence will be monitored using daily intake records and, where feasible, sachet counts/returns. If intolerance occurs (e.g., nausea, bloating, diarrhoea, or poor palatability), intake may be temporarily reduced to one pouch/day or divided into smaller portions, with re-titration to the target dose as tolerated; all dose modifications and reasons will be documented.

The dietary interventions will be delivered for 6 weeks, with participants receiving the intervention during their chemotherapy admission and home-based periods. The interventions will be supported through face-to-face visits, phone calls, and online communication (e.g., via WeChat). Dietitians, oncology nurses, and oncologists will support patients to ensure adherence to the protocol.

### Criteria for discontinuing or modifying allocated intervention/comparator {15b}

The allocated dietary intervention may be discontinued or modified for an individual participant if clinically indicated, including at the participant’s request, on the occurrence of a serious adverse event judged to be related to the intervention (e.g., food allergy or intolerance), or if the participant develops a medical condition that precludes safe continuation of the assigned diet (e.g., inability to maintain oral intake or a requirement for enteral/parenteral nutrition). Thereafter, the participant will receive standard clinical nutritional care as determined by the treating team, and the reason for discontinuation or modification will be documented. Discontinuation or modification of the allocated intervention will not automatically result in withdrawal from study follow-up; outcome assessments will be continued whenever possible.

### Strategies to improve adherence to intervention/comparator {15c}

Adherence will be promoted through structured education and ongoing support delivered by oncology nutrition specialists. At enrollment, participants will receive standardised written materials aligned with their allocated dietary programme, and key dietary targets will be explained to the participant and, where appropriate, a family caregiver. During the 6-week period, daily telephone/WeChat contacts will be used to record dietary intake (diet diary capture), reinforce the allocated strategy, and identify barriers (e.g., nausea, anorexia, oral mucositis, diarrhoea) that may affect intake. A prespecified checklist will be used to standardise contacts across groups. Participants will be asked to complete dietary records at prespecified time points; these records will be reviewed by the study team to assess adherence, provide feedback, and document deviations. For participants allocated to the oncology nutritional formula group, intake will be monitored by recording the number of servings consumed, and unused sachets will be returned or counted when feasible. For participants allocated to the plant-based diet programme, adherence will be assessed against the predefined dietary targets (e.g., plant food intake and restriction of red/processed meat) using dietary records and the plant-based diet index. The predefined targets include vegetables and fruits ≥ 500 g/d, whole grains 70–90 g/d with legumes consumed on most days, and red/processed meat ≤ 500 g/week (fish ≤ 300–450 g/week). Online group interactions will be used to maintain engagement, answer questions, and provide practical guidance (e.g., meal planning and preparation).

